### Recruitment

Patients will be recruited at Altnagelvin Area Hospital, Northern Ireland, having met the inclusion criteria and been fully informed of the study in the outpatient clinical setting. Within 14 days of surgery, patients will be reviewed and will be fully informed of the programme, and consent will be obtained. If the patient consents to participate in the study, they will undergo randomisation by the coordinating investigator as previously described. Patients may withdraw themselves at any time during the study; however, data up to this point will be included in any statistical analysis.

## Discussion

Patellar instability conveys significant morbidity to the young active population, which is further impacted in the case of recurrent instability [1–3]. There are multiple causes of patellar instability, some which require isolated soft tissue reconstruction, and others that require bony realignment surgery. Attempts to rationalize treatment with algorithmic evidence-based decision matrices have been published [3]; however, the multifactorial nature of the condition predisposes to confounding factors [17]. Using this information, we have developed the current trial in an attempt to create a homogenous population in order to assess two treatment options and minimise any confounding factors.

Previous studies have demonstrated appropriate outcomes using autologous hamstring and synthetic tape reconstruction. However, the majority of literature pertaining to these is of low quality, lacking in homogenicity, based on retrospective design and have potential recall and publication bias, as most are from high-volume centres [17, 38].

Berruto reported good increases in Kujala knee scores at 3 years following reconstruction using a bioactive synthetic ligament for MPFL reconstruction in 16 patients [26]. The authors also demonstrated a reduction in visual analogue scale pain scores compared to preoperative scores and an overall satisfaction rate of 88%. Risk of revision was low and this was for medial epicondylar pain.

Nomura and colleagues have extensive reported on the use of artificial ligaments for MPFL reconstruction. They have shown good outcomes in 27 knee joints, at a midterm follow up of 5.9 years, with a 96% satisfaction rate [25]. Furthermore, they have studied histological specimens and found that “ligamentization” occurs over time in the synthetic ligaments [39, 40]. In another study with a mean follow up of 11.9 years, an 88% success rate was reported with significant increases in the Kujala score from baseline, with minimal evidence of osteoarthritis in the long term [41].

This is the first study to directly compare autologous and synthetic grafts for MPFL reconstruction. The use of validated outcome scores, combined with a rigid study design, should allow definition of the indications for isolated MPFL reconstruction. Besides providing information on the reduction in pain, improvement in symptoms, the restoration of daily activities and the incidence of complication rates for MPFL reconstruction, the study will permit surgeons to fully inform patients requiring this intervention.

We present the rationale and design of a pragmatic randomised controlled trial in which patients are blinded to intervention allocation, comparing the use of autologous hamstring to synthetic ligament reconstruction, in patients with recurrent patellar instability due to confirmed disruption of the MPFL. The results of this trial will be beneficial for orthopaedic surgeons in defining the criteria for performing this surgery, and enable them to advise the optimal treatment choice for MPFL reconstruction. The first study results are expected in 2020 and will be communicated via publication and presentation at national and international meetings.

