## Methods

### Trial design

A single-centre, non-blinded, randomised control trial will be performed in Altnagelvin Area Hospital, Northern Ireland. This is a district general hospital with trauma and orthopaedic capabilities, serving the north and west of the province – a population of approximately 400,000 individuals.

The study aims to investigate the functional outcomes following MPFL reconstruction using either autologous hamstring reconstruction, or a synthetic open weave polyester tape (NeoLigament, Leeds, UK). This trial is not considered as a new interventional assessment, as both techniques are widely accepted and reported in the literature individually. However, no randomised controlled study has been performed evaluating these techniques head to head.

The study protocol (version 2) is registered with the ISRCTN (ISRCTN 16657952, March 2017), and contains the information required by the World Health Organisation Trial Registration Data Set.

Regional ethical approval was granted by the Office for Research Ethics Committees (REC) of Northern Ireland (ORECNI ID 17/NI/0129) on 21 August 2017.

The trial was designed using the Recommendations for Interventional Clinical Trials (SPIRIT) 2013 statement (Additional file 1). Figure 1 shows an example template of recommended content for the study. The Coleman Methodology Score (CMS) was used to assist with the trial design, ensuring validity and reliability of the study, and accordingly to allow for future meta-analyses [31]. The current CMS of the trial design is 79/100, equating to a rating of “good” (good 70–84, excellent 85+).

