### Intervention

The intervention will be reconstruction of the MPFL using either autologous gracilis or semitendinosus tendon, or synthetic open weave polyester tape (Neoligament, Leeds UK), with advancement of the vastus medius obliquitus (VMO). All surgery will be performed by the Principal Investigator, who is a consultant with significant specialist interest and expertise in soft tissue knee reconstruction, and who has performed significant numbers of both techniques. This will eliminate any learning curve between techniques. All patients will be reviewed preoperatively the by Principal Investigator to ensure eligibility for inclusion. Consent will be gained by the Principal Investigator or a suitably trained orthopaedic registrar, who is part of the clinical trial team.

Patients will undergo general anaesthetic for surgery. Routine intravenous antibiotic prophylaxis will be administered in accordance with local Trust policy. Patients will be positioned in a supine position with a high thigh-tourniquet. A side support is used to support the leg in 90° of flexion. Diagnostic arthroscopy will not be performed as all patients with evidence of an osteochondral lesion on preoperative MRI will be excluded from the study. Reconstruction using either a hamstring autograft or synthetic graft will be performed as per the surgeon’s default technique. Should there be a breach of the synovial lining, this will be repaired to ensure a purely extra-articular reconstruction is performed.

The autograft tendon will be harvested through an approximate 3-cm vertical incision over the pes anserinus with a vertical opening to the bursa and exposure and release of the tendon using a tendon stripper. The senior author’s preference is to use the gracilis tendon, unless it is of a poor quality, or if the patient body habitus requires a more substantial graft, then the semitendinosus tendon will be harvested instead.

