### Randomisation and blinding

The allocation to the surgical technique to be used will be placed in an opaque, sealed envelope by a study investigator. Once sealed, the envelopes will be randomly mixed before being numbered consecutively. No pre-stratification is required. The Principal Investigator will be blind to this process throughout.

Once the patient has arrived in the anaesthetic room of the operating theatre, the randomisation envelopes will be drawn in consecutive numerical fashion by the Principal Investigator and a member of the theatre team. This will determine which surgical technique the patient will receive. A master file containing a log of those involved in randomisation will be used for verification purposes.

Patients will be blinded to their study group at the time of entering theatre. It is not possible to blind the operating surgeon/Principal Investigator. No “sham” incisions will be used to blind the patients undergoing surgery to the intervention allocated. Unblinding will be permissible should patients present with a postoperative complication that requires repeat surgical intervention.

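### Blinding status is stated inconsistently, and the patient blinding claimed in the Discussion cannot be relied on when the patient-reported scores are collected

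*Protocol article*

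**What the plan says.** The protocol article describes blinding in three places.

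- **Trial design:** "A single-centre, non-blinded, randomised control trial will be performed". The label is not restricted to any party.
- **Randomisation and blinding:** "Patients will be blinded to their study group at the time of entering theatre". The section adds that the operating surgeon cannot be blinded and that sham incisions will not be used to mask patients. It then says: "Unblinding will be permissible should patients present with a postoperative complication that requires repeat surgical intervention".
- **Discussion:** the trial is a "pragmatic randomised controlled trial in which patients are blinded to intervention allocation".

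The timing of allocation is given in Randomisation and blinding: "Once the patient has arrived in the anaesthetic room of the operating theatre, the randomisation envelopes will be drawn in consecutive numerical fashion".

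The Intervention section gives one arm an additional wound: "The autograft tendon will be harvested through an approximate 3-cm vertical incision over the pes anserinus". The medial incision of about 6 cm is described without restriction to an arm, and no tendon harvest is described for the synthetic tape.

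Under Outcomes, the primary outcome is the patient-reported Kujala score. The Tegner, Lysholm, Banff Patellar Instability Index and ACL Quality of Life scores are collected at the same times: before surgery and at 3, 6, 12, 18 and 24 months after it.

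**The concern.** A reader cannot tell from the article who is blinded or for how long. As far as patients are concerned, the Trial design label and the Discussion claim cannot both be right. The Randomisation and blinding section does not settle the matter: one sentence confines blinding to a moment before surgery, and another presupposes that it continues after surgery.

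This matters because the primary comparison rests on what patients report about their own knee. The Abstract gives the rationale for a synthetic graft as sparing the hamstrings and avoiding donor-site morbidity, so a patient who knows the allocation could hold arm-specific expectations. If the trial is published as patient-blinded, readers will credit the Kujala comparison with a protection that the described procedures do not provide. So will the meta-analyses that the Trial design section hopes to feed.

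**Working it through.** No formula applies. The question is whether the statements agree, and whether the described procedures support the strongest of them. I took it in five steps.

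**1. Do the labels agree?** Trial design says non-blinded. Discussion says patients are blinded. One of the two must change, or be qualified by party and period.

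**2. What does blinding on entering theatre amount to?** The envelope is drawn only after the patient reaches the anaesthetic room. A patient entering theatre is therefore unaware of the arm because no envelope has yet been opened. That is concealment of allocation. It protects enrolment and the preoperative score, but says nothing about what the patient knows when later scores are given.

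**3. Is masking maintained after surgery?** The relevant features by arm, from Intervention and Randomisation and blinding, are:

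| Feature | Autograft | Synthetic |
|---|---|---|
| Medial incision, about 6 cm | yes | yes |
| Harvest incision over the pes anserinus, about 3 cm | yes | none described |
| Sham incision to match | not applicable | expressly not used |
| Other procedure to mask the patient | none described | none described |

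The wound pattern separates the arms. With 15 patients planned per arm, the described techniques would put a harvest wound on all 15 autograft patients and on no synthetic patient. This count describes the design. It does not measure bias.

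**4. Which outcomes are exposed?** All five postoperative score times fall after the wounds exist. The preoperative score precedes allocation. The analysis metric is change from preoperative baseline, so any effect of knowing the arm would enter through the postoperative score only.

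**5. Can the effect be sized?** No. The article gives no figure for expectation effects on the Kujala score, so nothing can be set against the 10-point difference used in the Sample size section. The direction is also open: a patient might favour the graft that spares the hamstrings, or the one made from their own tissue.

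The labels conflict (step 1), and the patient-blinding claim has no described procedure behind it for follow-up (steps 2 and 3). The exposed outcomes include the primary one (step 4).

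**The case against.** The strongest reply is that the Methods already disclose the position. The trial is labelled non-blinded, patient blinding is tied to entry into theatre, the surgeon is said to be unblinded, and the absence of sham incisions is stated openly. On that reading the plan is an unblinded trial with concealed allocation, and the overclaim is one clause in the Discussion plus the unblinding sentence. Much of this stands. Omitting a sham incision is a disclosed choice and is not criticised here. What does not stand is that disclosure in one section cures a contrary claim in another, particularly as the unblinding rule makes sense only if blinding continues after surgery.

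It could also be said that non-blinded refers to the surgeon alone. The Trial design section makes no such restriction. Even if it did, the Discussion claim would still lack a procedure to sustain it.

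A reader might go further and infer that patients know their graft as soon as they see the dressings, so that the trial is simply open-label. The documents do not establish that. Nowhere does the article say that patients are told their allocation. The Recruitment section says they are fully informed before consent, but not that incision sites are described to them. The wounds are covered with dressings, wool and crepe, and a brace is fitted. Later recognition of an extra wound is likely, but it remains an inference.

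A reader might also infer that the Kujala difference will be shifted by some definable amount. As step 5 shows, neither size nor direction can be derived.

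**Conclusion.** The concern holds in limited form. Blinding status is stated inconsistently across Trial design, Randomisation and blinding, and Discussion, and the design described does not secure patient blinding during follow-up. The primary and secondary patient-reported scores therefore carry a risk of bias of unknown size and direction. No sample size, test or estimate in the plan is altered.

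This is more than a clerical slip, because blinding status governs how far the primary comparison can be trusted. It should be corrected before results are reported.

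The conclusion assumes that the article's description of the wounds is complete and that no masking procedure exists elsewhere. If the full protocol contains one, the Discussion claim could be supported by describing it, but the conflict with the Trial design label would still need resolving.

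**What to change.** **Wording.**
- State once, and use consistently in all three sections, that allocation is concealed until the patient is in the anaesthetic room and that patients and surgeon are not reliably blinded afterwards.
- Remove the patient-blinding claim from the Discussion.
- Bring the unblinding sentence into line with that statement.
- Say that conclusions on patient-reported scores carry this limitation.

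**Low-cost safeguards.**
- Have patients complete the questionnaires themselves before contact with the unblinded surgeon at each review.
- Run the planned analysis, which a study investigator performs, on coded arms.

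These limit the influence of surgeon and analyst. They do not remove bias arising from the patient's own knowledge of the graft, so they do not replace the stated limitation. Complications and all-reason revision are already planned secondary outcomes, and nothing further is asked there.

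**Cost.** The trial reports a weaker blinding status and the clinic flow changes slightly. Surgery, allocation and sample size are untouched, so the changes remain feasible although the Trial status section reports that recruitment has begun.

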### Trial status

Patient recruitment and intervention began in January 2018.

## Abbreviations

ACL: Anterior cruciate ligament
BPII: Panff Patellar Instability Index
CMS: Coleman Methodology Score
CT: Computed tomography
EMS: Electromuscular stimulation
ISRCTN: International Standard Randomised Controlled Trials Number
MPFL: Medial patellofemoral ligament
MRC: Medical Research Council
MRI: Magnetic resonance imaging
ORECNI: Office for Research Ethics Committees of Northern Ireland
R&D: Research and development
RCT: Randomised controlled trial
REC: Research Ethics Committee
SPIRIT: Standard Protocol Items: Recommendations for Interventional Trials
SPSS: Statistical Package for the Social Sciences
VMO: Vastus medius obliquitus
